
### Study Procedures

#### Phase I:

The original CARE-CITE modules were designed as part of a CP-focused web-based intervention aimed to help the CP create a therapeutic home environment while encouraging the SS to use the weaker arm during functional tasks. We (SB, TK, SC, KB) modified the existing upper extremity CARE-CITE intervention to address gait rehabilitation. Collaborating with the University’s Center for Digital Scholarship, the video modules were redesigned with a progressive therapeutic exercise plan for home based functional task practice to improve overall mobility and stepping-related physical activity. Additional content was added to address safety risks/falls (appropriate use of gait belts, supervision, etc.) associated with gait and balance exercises. The gait revisions maintained the core CARE-CITE theoretical framework, which is the concept of autonomy support, with text and video that demonstrate ways to encourage empathy (video examples of discussions of CP with SS acknowledging the difficulty of the task), collaborating on problem-solving (examples of methods to increase or decrease the difficulty of activities together), emphasizing the importance of offering SS choice in activities to practice (examples of joint goal-setting) and ways to provide non-controlling language (scenarios showing controlling vs. non-controlling language).

We will follow similar procedures from our previous work, [21] identifying 6-8 content experts in stroke (rehabilitation researchers and clinicians with at least 5 years of experience) to evaluate the content validity and user satisfaction of the CARE-CITE-Gait intervention. We will identify 3 self-identified CPs of individuals with chronic stroke (> 3 months post-ischemic or hemorrhagic event) to review the CARE-CITE-Gait modules over two weeks and answer module feedback questions. Data gathered about CP user satisfaction and content experts content validity and user satisfaction will guide any additional refinements of intervention before initiation of Phase II study recruitment.

#### Phase II:

Table 1 depicts the schematic diagram of the study schedule and Figure 1 depicts the consort flow chart. The project coordinator will make a clinic appointment at Emory Rehabilitation Hospital for interested participants. If screening criteria are met, written informed consent will be obtained from the CP and SS by the study PI (SB) or project coordinator (HS). Medical clearance from the SS physician will be obtained before study participation. Double baseline data collection visits will be conducted in the clinic/lab, one week apart, by the research evaluator (licensed physical therapist) blinded to the content of CARE-CITE-Gait intervention. Following the second baseline data collection, the research interventionist (licensed physical therapist) will schedule dyads for the Week 1 (orientation) and Week 4 home visits and complete Week 2 and 3 phone calls. The project coordinator will schedule all dyad data collection appointments. All dyads return to the clinic for the post-test, and 1-month follow-up visits. Accelerometers (wearable sensor) data will be gathered between the first and second baseline assessments (pre-training), and after the post, and 1-month follow-up assessments. Accelerometers will be worn for all activities for a minimum of 3 days up to a target of 7 days, except for water-based activities. We will provide SS with wearable sensors and instructions regarding compliance and data logging for sensor-based activity data.

### Data management and analysis

REDCap (Research Electronic Data Capture)[37] electronic database will be used to store the quantitative data. REDCAP is a secure (compliant with United States healthcare confidentiality legislation requirements), web-based application designed to support data capture for research studies, providing 1) an intuitive interface for validated data entry; 2) audit trails for tracking data manipulation and export procedures; 3) automated export procedures for seamless data downloads to common statistical packages; and 4) procedures for importing data from external sources. The project coordinator will be trained in REDCap processes and will complete all data entry. Data will be double checked for verification by a second REDCap trained research assistant. REDCap creates a comma separated value file and SAS program to create an analytic dataset. These files and all resulting datasets, programs, and results are stored on a HIPAA compliant Rollins School of Public Health sever.

Standard data cleaning, identification of missing data, and internal consistency reliability for standardized scales will be completed. We will investigate whether missing data is related to treatment and baseline factors but do not anticipate missing data being a limitation if lost-to-follow-up rates in this new clinical trial are similar to other stroke studies performed in the PI (SB) and Co-I (TK) labs. Primary quantitative statistical analyses will be performed by the study statistician (GC) using SAS statistics for Windows (Version 9.4) and accelerometry data analysis (SS stepping activity) will be performed by lead research assistant (RS) using ActiLife software (Version 6.13.4). Descriptive statistics (e.g., frequencies, means, ranges, standard deviations) will be calculated for all relevant variables, as well as to identify unusual or suspect values requiring review and confirmation. Additional descriptive statistics will be calculated for feasibility measures of recruitment rate, retention, and CP usability and satisfaction with CARE-CITE-Gait (described under Feasibility section). To determine estimates of variability (for postulating effect sizes to design next phase clinical trials, the mean and median changes from baseline to one month and standard errors of the means will be calculated. To provide preliminary information about possible feasibility study intervention effects, confidence intervals for the difference in mean changes for major study variables will be reported as descriptive statistics. Graphical methods will be used to investigate outliers and investigate the consistency of the changes over time. Estimates of inter-correlations among the study variables will be calculated to gain insight into potential variables that could influence response to the intervention and guide the design of future studies. To understand potential relationships and possible confounding factors we will examine SS co-morbidities (e.g., history of testing positive for COVID) and the biological variables of CP age, sex, gender and relationship of CP to SS (e.g. spouse, adult child). The second phase of the analysis will include one-way repeated measures analysis of variance (ANOVA) to evaluate differences between baseline, post, and follow-up timepoints. Tukey’s pairwise comparisons will be used to determine which time points are different if necessary. Level of significance of 0.05 will be used. No adjustments will be used to control for multiple study variables.

### Auditing

All research records will be available for review by authorized representatives of the Foundation for Physical Therapy Research, regulatory agencies and the University Institutional Review Board to monitor study safety, progress, and procedures for quality assurance.

### Dissemination

Dissemination of study results to academic communities will occur through peer-reviewed manuscripts and regional and national conference presentations. The study team will work collaboratively with the funding agency to share results based on agency requirements. The PI will meet regularly with the study team to revise the proposed dissemination plan and discuss authorship guidelines. For non-academic communities, the PI will schedule presentations with community stroke groups and therapy clinics involved in study recruitment. A lay summary of study findings will be created for distribution based upon participant requests.

## Discussion

This protocol describes the methodology to evaluate the feasibility of a CP-integrated telehealth gait rehabilitation program during stroke recovery. The study findings will provide valuable insights regarding innovative home-based rehabilitation that engages CPs and support a future study testing the efficacy of CARE-CITE-Gait intervention. Results will provide important preliminary estimates of efficacy and components of variability as well as inform future randomized clinical trial sample size power calculations. Data gathered regarding recruitment, retention, and adherence rates, adverse events, outcome measure appropriateness and participant exit interviews will inform the feasibility and justification of a definitive trial of CARE-CITE-Gait. Our proposal will lay foundations for several research trajectories with the long-term goal of developing more personalized, precise, and efficacious family-focused rehabilitation interventions.

## Trial Status

This trial was registered on clinicaltrials.gov (NCT 05257928) on March 25, 2022. Recruitment of participants was initiated on May 18, 2022. To date, we have recruited 90% of the participants.

## Figures and Tables

**Figure 1 F1:**
[figure not shown]
Consort Flow Chart: Evaluation of a Carepartner-Integrated Telehealth Gait Rehabilitation Program for Persons with Stroke (CARE-CITE-Gait) (N=5). [see attachment]

**Table 1: T1:** CARE-CITE-Gait study schedule.

	STUDY PERIOD								
				CARE-CITE-Gait Intervention					
	Screen	Baseline 1	Baseline 2	Week 1	Week 2	Week 3	Week 4	Post Intervention Evaluation	1-month Follow-up Evaluation
Eligibility screen	PC								
Informed consent		PI							
Medical history (including COVID questionnaire)	x	x	x (updates)					x (updates)	x (updates)
Demographics		x							
SS Vitals (BP, HR, O_2_ saturation)		x	x	*			*	x	x
SS 10-meter walk test		x	x	*			*	x	x
SS 6-minute walk test		x	x					x	x
SS 5STS		x	x	*			*	x	x
SS TUG		x	x	*			*	x	x
SS SIS		x						x	x
SS FCCQ-SS		x	x					x	x
SS ABC		x	x	*			*	x	x
SS Accelerometry (3-7 days)		x	x					x	x
CP CSI		x	x					x	x
CP FCCS		x	x					x	x
CP BCOS		x	x					x	x
CP FCCQ-CP		x	x					x	x
CP CCG Module Feedback questions				CP			CP		
CP CCG Module Reflection questions				CP			CP		
CP PSSUQ									x
CP Exit Interview									x
Adverse events monitoring		*							*

SS-stroke survivor, CP-carepartner, CCG-CARE-CITE-Gait, BP-blood pressure, HR-heart rate, O_2_-oxygen saturation, 5STS-5-times Sit to stand, TUG-Timed up and go test, SIS-Stroke Impact Scale, FCCQ-SS-Family Care Climate Questionnaire for stroke survivor, ABC-Activities-Specific Balance Confidence Scale, CSI-Caregiver Strain Index, BCOS-Bakas Caregiving Outcomes Scale, FCCS-Family Caregiver Conflict around Stroke Recovery Scale, FCCQ-CP - Family Care Climate Questionnaire for carepartner, PSSUQ-Post Study System Usability Questionnaire PC-completed by project coordinator, PI-completed by PI, x-completed by evaluator

* completed by intervention therapist

**Table 2. T2:** Content of the CARE-CITE-Gait Intervention for the Carepartner

Modules	Content
Overview of Modules Structure	Each module has multimedia to provide the purpose, educational content, and/or illustrate examples of the topics discussed. Concluding each module, 4-5 reflection questions are provided to allow for application of content and 7 feedback questions are provided to gather information on ease-of-use, acceptability, and usefulness of modules.
Module I: Introduction to CARE-CITE-Gait	Describes CARE-CITE Gait project and defines the roles of the CP and SS and summarizes the modules. Welcome survey provided for CP to complete with research interventionist for practice using the website and answering questionnaires.
Module II: Introduction to Carepartner and Collaborative Integrated Therapy – CARE-CITE	Overview of goal setting (providing examples in the areas of household activities of daily living, leisure, and work-related, and collaborative activities), home diary (to record activities and difficulty level), and review of safety measures and behavior contract (use of gait belt, agreement between stroke survivor and carepartner on individual and collaborative activities). Two videos showing examples of practicing activities of daily living to improve balance and gait, image examples of a completed home diary and behavior contract, and seven videos of conversations around safety and considerations.
Module III: Practice and Goal Setting	Review of role of practice in promoting neuroplasticity and recovery after stroke. Discussion of collaborative problem-solving to accomplish tasks, maintaining appropriate challenge threshold, both reducing task complexity when a task is too difficult and increasing challenge when the task is easily mastered. Two to seven video clips capture each of the six themes of practice.
Module IV: Autonomy Support – Creating Partnerships	Cultivating an autonomy supportive environment with empathy, problem-solving through tasks in the home setting, use of non-controlling language, and offering choice. Recognize challenges and explore ways to improve communication (avoid controlling language such as “you should exercise,” or “you have to do this”). Eight video clips illustrate understanding another’s viewpoint, using problem-solving strategies, providing rationale, and providing choice during gait and mobility exercises.
Module V: Taking Care of Yourself as a Carepartner	CP self-care – recognizing demands of caregiving role, strategies for stress reduction, opportunities for self-care activities and community resources (only text).
Module VI: Reflections	Six videos (limited text) of stroke survivors and CP reflecting on rehabilitation and recovery. Encouraging CP reflection on his/her role in recovery of the individual with stroke.

**Table 3: T3:** CARE-CITE-Gait Study Feasibility Outcomes

Outcome	Definition
Recruitment	Recruitment rates will be the percentage of those participants enrolled and randomized from those screened. Recruitment will be deemed feasible if the target enrollment of 15 dyads (2-3 dyads per month) is reached during the study timeframe.
Retention	Retention of participants will be the percentage of dropouts. An acceptable retention rate will be 85% of enrolled participants for completion of post-evaluation (80% for one-month follow-up).
Intervention Adherence*	CP adherence will be the number of modules reviewed (6 total modules) as indicated by the reflection questions completed at the end of each section. Criteria for CP adherence will be a minimum completion of 5 of the 6 modules. *Study staff are electronically notified of module completion in real-time which allows for reminders to be sent to participants to review modules as needed*. Criteria for CP and SS adherence will be >3.5 hours (for two home visits) and CP completion of week 2 and 3 phone calls.
Safety	Number and type of adverse events (serious vs. non-serious; related or possibly related to CARE-CITE-Gait

* Adherence to the intervention will be evaluated only in the participants completing a baseline and a post-intervention evaluation. SS-stroke survivor; CP-carepartner

**Table 4. T4:** Outcome measures collected at baseline, post-intervention, and 1-month follow-up

Variable	Measure	Description	Reliability/Validity
SS Gait Speed*	10-meter walk test^32^	Time to complete a standardized overground distance; correlated with functional ambulation categories	Excellent test-retest (ICC>0.95),[38] intra- and inter-rater reliability (ICCs>0.87); established construct [39]and criterion[40] validity in stroke
SS Endurance	6-minute walk test^33^	Distance walked in 6-minutes; measure of aerobic capacity and long-distance walking function	SEM, MDC, and MCID published in older adults and stroke; excellent reliability (ICC>0.99); validity established in stroke[39, 41, 42]
SS Dynamic Balance and Functional Mobility*	5-times Sit to stand (5STS)^34^ Timed up and go test (TUG)^35^	Timed tests of functionally relevant lower limb activities (sit to stand, walking, turning)	5STS - Criterion validity with leg muscle strength in stroke; discriminates stroke versus able-bodied;[43, 44] [45] TUG – SEM, MDC, reliability, validity published in stroke[39, 46, 47]
SS Quality of Life	Stroke Impact Scale (SIS)	59-items, 8 domains function	Test-retest reliability ICC = 0.70 to 0.92; Internal consistency alpha coefficient of 0.83-0.90 [48]
SS Mobility Confidence*	Activities-Specific Balance Confidence Scale (ABC)	16 items, self-report of balance confidence with balance-related activities	Adequate to excellent test-retest reliability for total score ICC=0.85), excellent internal consistency[49, 50]
SS Average stepping activity**	Wearable sensors (Actigraph^38^)	Actigraph GT3X+ *(Actigraph Pensacola, Florida, USA)* triaxial accelerometer; raw acceleration data are converted into activity counts per minute.	Step activity monitors have been shown to have excellent test-retest reliability on 3-day monitoring (ICC>0.9); criterion validity published in stroke [51] [52–54]
CP/SS Autonomy Support Environment	Family Care Climate Questionnaire FCCQ-CP/FCCQ-SS	14-item, Likert-type scale. Higher scores/higher autonomy support perception	Internal consistency >. 70; Construct validity supported- higher FCCQ-SS scores related to SS lower perception of criticism, higher family emotional involvement-higher satisfaction with family support (p ≤ .05)[55]
CP Strain	Caregiver Strain Index - CSI (modified)	13-item questionnaire, binary yes/no; higher score/higher strain	Good reproducibility and validity in stroke carepartners, Cronbach’s alpha of .83 [56–59]
CP Family Conflict	Family Caregiver Conflict Scale (FCCS) about Stroke Recovery	15-item, Likert-type scale Higher scores/higher conflict	Established content/construct validity in stroke CP; reliability Cronbach’s alpha of .93[60]
CP Well-being related to Caregiving	Bakas Caregiving Outcome Scale (BCOS)	15-items; 7 point scale; higher scores/more positive caregiving outcomes	Satisfactory reliability and validity in stroke carepartner, Cronbach’s alpha of .90 [61]
CARE-CITE-Gait Usability							
CP experience in CARE-CITE	Exit Interview questionnaire	Three sections assessing confidence in care, value of participation and aspects of CARE-CITe	Interview guide will be reviewed by content and qualitative experts prior to use.
CP satisfaction with CARE-CITE	Feedback forms at end of CARE-CITE modules	5-items, Likert-type scale; higher scores/higher satisfaction	Interview guide will be reviewed by content and qualitative experts prior to use.
CP experience using CARE-CITE	Post Study System Usability Questionnaire (PSSUQ)	19-item, Likert-type scale. Lower scores/greater usability of instrument	Established reliability and validity[33]

SS-stroke survivor, CP-carepartner, CCG-CARE-CITE-Gait, BP-blood pressure, HR-heart rate, O_2_ – oxygen saturation, 5STS-5-times Sit to stand, TUG-Timed up and go test, SIS-Stroke Impact Scale, FCCQ-SS-Family Care Climate Questionnaire for stroke survivor, ABC-Activities-Specific Balance Confidence Scale, CSI-Caregiver Strain Index, BCOS-Bakas Caregiving Outcomes Scale, FCCS-Family Caregiver Conflict around Stroke Recovery Scale, FCCQ-CP - Family Care Climate Questionnaire for carepartner, PSSUQ-Post Study System Usability Questionnaire PC

* additional administration during home visit week 1 and week 4

** accelerometers worn at home for 7 days

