### Study Design & Setting

In Phase I, stroke rehabilitation content experts and CPs will evaluate the usability and acceptability of the CARE-CITE-Gait modules. In Phase II, feasibility (based on measures of recruitment, retention, and intervention adherence) and preliminary effects of CARE-CITE-Gait will be measured using a one-group, quasi-experimental design with repeated measures (two baseline visits one week apart, post-test, and one-month follow-up) with 15 CP and SS dyads. While the in-person portion of the intervention will take place in participant homes, the study recruitment, screening, and evaluations (evaluator-blinded) for CP and SS dyads, will occur in a stroke research laboratory within an urban rehabilitation hospital located in Atlanta, Georgia, United States (Figure 1 Consort Flow Chart: Evaluation of Carepartner-Integrated Telehealth Gait Rehabilitation Program for Persons with Stroke (CARE-CITE-Gait) N=15)). Licensed physical therapists will conduct the evaluations and administer the 4-week home-based CARE-CITE-Gait intervention. During the intervention period, the web-based CARE-CITE-Gait modules will be accessed online by CPs independent of therapist involvement. The study schedule schematic design is presented in Table 1.

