#### Sample size estimation

For Phase II, given the time required to adapt the intervention, the proposal timeline, and preliminary data from our upper extremity intervention, a sample size of 15 dyads is proposed to evaluate feasibility (2-3 dyads/month). An attrition rate of ~8% is projected based on the literature and our previous work [30]; thus, we will enroll 16 dyads to achieve a final sample of 15. Assuming a two-tailed alpha=0.05, we will have 80% power to detect an effect size=0.78 (Cohen, large), and can calculate 95% confidence intervals within 0.64 standard deviations. These data will provide precision to the estimates of mean changes, variability, and effect sizes for key outcomes. Importantly, these data will inform sample size estimation and identify feasibility lessons to guide our planned next step - a randomized clinical trial evaluating the efficacy of CARE-CITE-Gait.

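### Table 3 misdefines the retention and recruitment rates, and its recruitment target of 15 dyads conflicts with the planned enrolment of 16

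*Protocol article*

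**What the plan says.** The Feasibility section of the protocol article refers the reader to Table 3 for the definitions and success criteria of the feasibility outcomes. It also equates enrolment with signed consent.

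- **Retention (Table 3).** The definition and the criterion stand together: "Retention of participants will be the percentage of dropouts. An acceptable retention rate will be 85% of enrolled participants for completion of post-evaluation". For the one-month follow-up the figure is 80%.
- **Recruitment rate (Table 3).** "Recruitment rates will be the percentage of those participants enrolled and randomized from those screened".
- **Recruitment criterion (Table 3).** "Recruitment will be deemed feasible if the target enrollment of 15 dyads (2-3 dyads per month) is reached during the study timeframe".
- **Design (Study Design & Setting).** Phase II is a "one-group, quasi-experimental design with repeated measures".
- **Planned enrolment (Sample size estimation).** "An attrition rate of ~8% is projected based on the literature and our previous work", and "thus, we will enroll 16 dyads to achieve a final sample of 15". The same paragraph states 80% power for an effect size of 0.78 at two-tailed alpha 0.05.
- **Participants section.** It gives 15 as the number of dyads to be recruited for Phase II, in agreement with Table 3 and not with the sample size section.

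**The concern.** Recruitment and retention are primary outcomes here, so their definitions should be usable as written. Three things are not.

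1. The quantity named retention is the dropout percentage. A report that follows the definition would put a small number under that name, beside a threshold meant for a large one.
2. The recruitment numerator requires randomization, which this design does not contain.
3. The recruitment criterion is satisfied at an enrolment that the sample size section treats as one dyad too few.

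The Discussion says that the recruitment and retention data will inform a definitive trial. A mislabelled retention figure, or a recruitment rate with an unclear numerator, would carry over into that planning. The third point affects whether recruitment can be called feasible when enrolment stops short of the plan's own number.

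**Working it through.** **Inputs.** Final sample 15, planned enrolment 16, attrition about 8%, effect size 0.78, two-sided alpha 0.05 and power 80% (Sample size estimation); thresholds 85% and 80%, target 15 dyads, 2 to 3 dyads per month (Table 3).

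**The plan's own figures.** Inflating for attrition: 15 / (1 − 0.08) = 15 / 0.92 = 16.3. The plan states 16, which is this figure rounded down; rounding up would give 17. For power I assume a paired (one-sample) t-test, since the paragraph names no test. With n = 15 and d = 0.78 the power is 0.802, so the stated 80% reproduces.

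**Retention.** Taken literally, an 85% dropout percentage among 16 dyads means 0.85 × 16 = 13.6, so 14 dropouts and 2 completers. That cannot be meant, and the next sentence of the table rules it out. With retention as completers over enrolled, the thresholds translate as follows:

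| Enrolled | Completers needed at post-evaluation (85%) | Completers needed at one month (80%) |
|---|---|---|
| 15 | 12.75, so 13 (86.7%) | 12 (80.0%) |
| 16 | 13.6, so 14 (87.5%) | 12.8, so 13 (81.3%) |

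**Recruitment rate.** The numerator requires both enrolment and randomization. In a one-group study the number randomized is 0, so the literal rate is 0% however many dyads are screened. The pass/fail rule does not use this rate; it uses the count of 15 dyads.

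**15 against 16.** Because enrolment means signed consent, the 15 in Table 3 cannot be read as 15 completers. Suppose each dyad stays independently with probability 0.92:

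- 15 enrolled: expected completers 15 × 0.92 = 13.8. Chance that all 15 complete: 0.92^15 = 0.286.
- 16 enrolled: expected completers 16 × 0.92 = 14.72. Chance of at least 15: 0.92^16 + 16 × 0.92^15 × 0.08 = 0.263 + 0.366 = 0.630.

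**Effect on the power statement.** At d = 0.78, power is 0.802 with 15 completers, 0.770 with 14 and 0.733 with 13. The effect detectable with 80% power moves from 0.778 at n = 15 to 0.810 at n = 14.

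**Time.** At 2 to 3 dyads per month, 15 dyads take 15/3 to 15/2, or 5.0 to 7.5 months; 16 take 16/3 to 16/2, or 5.3 to 8.0 months.

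**The case against.** A reader might infer that Table 3 inverts the retention verdict and leaves the recruitment verdict undefined. The document does not support either reading. The retention criterion gives its numerator (those completing the evaluation), its denominator (those enrolled) and its thresholds in the sentence directly after the faulty definition, and dropout is simply 100% minus retention. The recruitment percentage carries no threshold, so removing the reference to randomization changes no decision. Both replies stand. They limit the fault to what is defined and reported.

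A reader might also infer that 16 dyads cannot deliver 15. That is mostly rounding. The attrition figure is approximate, 16 enrolled gives exactly 15 expected completers at 1/16 = 6.25% attrition, and even at 8% a final sample of 15 or more is more likely than not (63%).

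On 15 against 16, it can be argued that a recruitment criterion need not equal the over-enrolled number, because attrition is judged separately under retention. It can be added that the power statement serves the secondary objective, where confidence intervals are reported descriptively. This has force: the loss is one dyad and the change in detectable effect is small. It does not remove the contradiction, because no passage says that 15 is the criterion and 16 an allowance. The sample size section says 16 will be enrolled; the Participants section and Table 3 say 15. The Trial Status section reports 90% of participants recruited without saying of which number.

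Finally, with recruitment that far advanced, raising a success threshold is a late change. That is a reason to allow either way of reconciling the numbers.

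**Conclusion.** The point holds as a should-fix. Two primary feasibility measures are wrong as written: retention is defined as its complement, and the recruitment rate has an impossible numerator. Neither error changes a pass/fail result for a reader who applies the stated thresholds. The recruitment criterion conflicts with the sample size section by one dyad. At 8% attrition that is 13.8 against 14.7 expected completers, and a 29% against a 63% chance of 15.

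These figures assume independent dropout between dyads at exactly 8%, and the power figures assume a paired t-test. The textual conflicts rest on no assumption.

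**What to change.** In Table 3:

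- Define retention as enrolled dyads completing the post-evaluation (or the one-month follow-up) divided by enrolled dyads, acceptable at 85% or more (80% or more).
- Define the recruitment rate as dyads enrolled divided by dyads screened, and delete the reference to randomization. Using dyads in both rows also removes the mix of participants and dyads.

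Across the Participants section, the Sample size estimation section and Table 3, reconcile 15 and 16. Either align the recruitment criterion with the planned enrolment of 16, or state that 15 is the criterion and 16 includes the attrition allowance. Date the choice, and make it before results are judged against it.

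In the sample size section, give the expected final sample as about 14.7 (14 to 15) dyads.

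The cost is a few words in a table and one figure in a paragraph. No extra dyads beyond the planned 16 are needed. If the first option is taken, the criterion becomes one dyad stricter, which at the planned pace adds 0.3 to 0.5 months (5.3 − 5.0 and 8.0 − 7.5) to the time needed to meet it.
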